## Methods and design

The study is being conducted at the Institute of Oncology Ljubljana in collaboration with the Slovenian Institute for Transfusion Medicine, the Clinic of Nuclear Medicine at the University Medical Centre Ljubljana, and the Institute of Biochemistry and Molecular Genetics at the Faculty of Medicine, University of Ljubljana. It is a non-randomized, single-center, open-label, phase I exploratory study. The study will include 10 patients (intervention group) and 10 healthy volunteers (control group) (Figure 1).

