**FIGURE 1. j_raon-2023-0052_fig_001:**
[figure not shown]
Design of the clinical trial. CTCAE v5 = Common Terminology Criteria for Adverse Events version 5.0; MRI = magnetic resonance imaging; MSC = allogeneic mesenchymal stromal stem cells; RT = radiotherapy; SCC = squamous cell carcinoma; US = ultrasound; [99mTc]*HMPAO* = Technetium 99m-hexamethylpropyleneamine oxime; [99mTc]TcO_4_ = Technetium 99m-pertechnetate

The aim of the study is to evaluate the safety and preliminary efficacy of treatment of xerostomia after irradiation with allogeneic MSC from umbilical cord tissue. Thus, we hypothesize that the treatment of post-radiation xerostomia with allogeneic MSC from umbilical cord tissue is safe and effective.

The study protocol was approved by the National Medical Ethics Committee (No. 0120-193/2023/3) and registered in the ClinicalTrial.gov database (NCT06012604) under the title: “*Treatment of Post-radiation Xerostomia with Allogeneic Mesenchymal Stromal Stem Cells: A Pilot Study”,* registered on 22 August 2023; https://classic.clinicaltrials.gov/ct2/show/NCT06012604

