### Pre- and post-treatment assessment

After being informed about participation in the study and signing the Informed Consent form, patients will undergo the following tests and complete the following questionnaires during the 4-week period before MSC application, i.e., the procedure (Table 3). The same measurements will be performed and questionnaires completed at both the 4-week and 4-month follow-up, with the exception of core needle biopsy and salivary gland scintigraphy (these will be repeated only at the 4-month follow-up). All procedures in the study are listed in Table 3.

**TABLE 3. j_raon-2023-0052_tab_003:** Procedures of the study

**Procedures**	**Inclusion**	**Intervention**	**Follow-up examinations**			

	**W4→0**	**D0**	**D1**	**D5**	**D28**	**D120**
Patient screening with clinical and objective evaluation of xerostomia^1^	X					
Complete blood count, biochemistry	X				X	X
Coagulation profile	X					
Measurement of unstimulated and stimulated salivary flow rate	X				X	X
Determination of salivary composition	X				X	X
Magnetic resonance imaging	X				X	X
US elastography	X				X	X
Scintigraphy with [99mTc]Tc-HMPAO labeled MSCs		X				
Scintigraphy with (*[99mTc]TcO_4_^−^*)	X					X
Core needle biopsy of the gland^2^	X					X
Visual Analog Scale questionnaire	X				X	X
Xerostomia Questionnaire	X				X	X
EORTC QLQ-H&N35	X				X	X
Toxicity assessment, CTCAE v.5		X	X	X	X	X

CTCAE v.5 = Common Terminology Criteria for Adverse Events version 5.0; D = day; EORTC QLQ-H&N35 = European Organisation for Research and Treatment of Cancer Quality of Life Questionnaire Head and Neck Module; MSCs = allogeneic mesenchymal stromal stem cells; US = ultrasound; W = week; [99mTc]*HMPAO = T*echnetium 99m-hexamethylpropyleneamine oxime; *[99mTc]TcO_4_^−^* = *T*echnetium 99m-pertechnetate

1 Inclusion criteria, see Table 2.

2 From the parotid gland: the first 5 patients included in the study; from the submandibular gland: the last 5 patients included. The gland on the side that received a higher dose of radiation will be punctured.

The study also involves 10 volunteers (control group) who do not participate in the procedure. They will sign the Informed Consent to Participate in the Study and provide saliva samples for the measurement of unstimulated and stimulated salivary flow and for the determination of salivary composition (for comparison with the intervention group).

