### Course of the study

After the procedure (day 0), patients (intervention group) will be examined at day 1, day 5, after 4 weeks, and after 4 months. An assessment of toxicity will be performed at each visit. At 4 weeks and 4 months after the intervention, the same measurements and questionnaires will be performed as when patients were enrolled in the study, except for core needle biopsy and scintigraphy, which will be repeated only at 4 months (Figure 1).

No follow-up is scheduled for the volunteers (control group) after enrollment in the study and the initial examinations (day 0).

The study will continue until completion of follow-up for the last enrolled patient or for a maximum of two years. Tentatively, the study is expected to run from October 2023 to September 2025.

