### Statistical methods

Since this is an exploratory study, no formal sample size calculation was performed.

Data will be managed in databases with Excel spreadsheets and analyzed with statistical analysis software such as SPSS, GraphPad Prism, or similar tools. Changes in absolute values and percent deviations from baseline salivary flow rate values before and after the procedure will be analyzed and compared at different time points within the intervention group; baseline values will also be compared with those of the control group. Numeric variables will be compared with paired t tests or nonparametric tests if the assumptions for parametric tests are not met.

The scores of the individual items of the VAS questionnaire and the Xerostomia questionnaire will be summed, and the total score is linearly transformed into a scale from 0 to 100.^29,30^ Scoring and interpretation of the EORTC QLQ-H&N35 questionnaire will be performed according to EORTC guidelines.^31^

Comparisons of MRI, ultrasound, scintigraphy, and analysis of core-needle biopsies taken before and after procedure will be descriptive in nature.

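### The only test named is the paired t test, which does not fit the comparison of patients' baseline values with the healthy volunteers

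*Protocol article*

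**What the plan says.** The Statistical methods section of the protocol article sets two comparisons. Salivary flow is to be analysed before and after the procedure, "compared at different time points within the intervention group". The same sentence then brings in the volunteers, and the next sentence gives the test: "baseline values will also be compared with those of the control group. Numeric variables will be compared with paired t tests or nonparametric tests", the latter where parametric assumptions fail. The test sentence applies to numeric variables in general. The nonparametric alternative is not named, and no two-sample test appears anywhere in the article.

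On who is being compared, the Pre- and post-treatment assessment section says: "The study also involves 10 volunteers (control group) who do not participate in the procedure". That section adds that their saliva is collected to compare flow and composition with the patients. Methods and design gives 10 people in each group. According to Course of the study, the volunteers are examined once and not followed up.

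**The concern.** The before-after comparison has natural pairs, because each patient is measured again. The comparison with volunteers has none: the article describes no rule that links a given patient to a given volunteer. A paired t test works on within-pair differences, so without defined pairs its result depends on which volunteer stands in which row. Because both groups have 10 members, software will run the test without complaint and take the spreadsheet order as the pairing.

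Two analysts with the same 20 values could therefore report different p-values. The test also works with 9 degrees of freedom where an independent-samples test has up to 18, which costs some power. At stake is the comparison of patients with healthy people on salivary flow and on the six composition measures (pH, total protein, amylase, MUC1, esterase, paraoxonase).

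**Working it through.** The plan gives no sample-size, power or alpha figure for this comparison, so there is nothing to reproduce. The size of the problem can only be illustrated.

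**Inputs from the article.** 10 patients and 10 volunteers (Methods and design); patients' unstimulated flow between 0.05 and 0.20 ml/min (Table 2).

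**Assumptions.** Two-sided 5% level; volunteer means and SDs as listed below; patient values spread evenly over the eligible range (mean 0.125, SD 0.0454 ml/min).

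**1. One data set, different row orders.** Take a volunteer mean of 0.20 and a nominal SD of 0.10 (0.0989 in the 10 constructed values). The mean difference is 0.200 − 0.125 = 0.075 whatever the order. Only the SD of the differences changes, with t = 0.075 / (SD of differences / √10).

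- Both groups sorted upwards: SD 0.0542, t = 0.075 / 0.01713 = 4.38, 9 df, p = 0.002.
- One group reversed: SD 0.1440, t = 0.075 / 0.04554 = 1.65, 9 df, p = 0.134.
- Independent samples: standard error √(0.0454²/10 + 0.0989²/10) = 0.0344, t = 2.18, p = 0.043 (Student, 18 df) or 0.049 (Welch). This does not depend on order.

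**2. Range over volunteer assumptions** (10,000 random pairings for the last column).

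| Volunteer mean / SD (ml/min) | Paired p, sorted to reversed | Welch p | Random pairings with p < 0.05 |
|---|---|---|---|
| 0.18 / 0.08 | 0.0007 to 0.195 | 0.077 | 17% |
| 0.20 / 0.10 | 0.002 to 0.134 | 0.049 | 39% |
| 0.25 / 0.12 | 0.0005 to 0.039 | 0.009 | 100% |
| 0.35 / 0.15 | 0.00007 to 0.005 | 0.0008 | 100% |

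In the last two rows the order changes the p-value but not the conclusion.

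**3. Power with an arbitrary order fixed in advance.** For a true difference of d SDs and n = 10 per group, both tests have noncentrality d × √(n/2) = d × √5. The critical values are 2.262 (9 df, paired) and 2.101 (18 df, independent).

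- d = 1.0: noncentrality 2.24; power 51% paired, 56% independent.
- d = 1.3: noncentrality 2.91; power 74% paired, 79% independent.

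**4. Type I error** (20,000 simulated data sets with no true difference). It is 0.050 for a pairing fixed in advance and 0.051 for the independent test. Sorting both groups by value before pairing raises it to 0.47, but nothing in the plan suggests that this would be done.

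**5. How often the order matters.** At a true difference of 1 SD, re-pairing the same data moves the paired p-value from about 0.01 to 0.10 (5th to 95th percentile of pairings, typical data set). How often the 0.05 conclusion changes depends on the counting rule. At least one of 400 random pairings crosses 0.05 in roughly 60% of data sets. At least 5% of pairings fall on each side in roughly 45%. On average about 11% of pairings disagree with the majority. The share with any crossing falls to 10% at 2 SD and to none at 3 SD.

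**The case against.** The strongest reply is that the wording is merely loose. Most of the preceding sentence concerns change over time within patients, where pairing is right; the volunteer comparison is an added clause, and the unnamed nonparametric tests could include a rank-sum test. The article never says outright that patients will be paired with volunteers. That is a fair account of what may have been meant. It does not remove the point, because the sentence covers numeric variables without restriction and names no other parametric test.

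The reply on size stands. A pairing fixed in advance does not inflate false positives, the loss of power is about 5 percentage points, and the effect fades as the true gap grows. Unstimulated flow may well show a large gap, since patients are admitted only at or below 0.20 ml/min.

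A reader might infer two stronger criticisms. The first is that the volunteers are unmatched and unselected on age, sex, smoking or medication. The article gives no volunteer criteria, but a condensed article commonly leaves these to the full protocol, so its silence does not show that none exist. The second is that the control group fails to support the hypothesis that the treatment is effective. The Statistical methods section uses the volunteers only for a baseline comparison, Table 1 places efficacy in the patients' own measurements over time, and nowhere is efficacy drawn from the volunteers.

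**Conclusion.** The point holds as a mismatch between a stated test and a stated comparison. Read as written, the plan applies a paired t test to two groups of different people with no pairing described, and the p-value would then rest on row order.

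The consequence is small: about 51% against 56% power at a 1 SD difference, with type I error held at 5% if the order is set beforehand. It would be noticed mainly for composition variables with moderate differences. These sizes rest on assumed volunteer distributions and an assumed 5% level, since the article gives neither. The comparison is secondary in an exploratory study whose primary objective is safety, and neither the safety results nor the before-after results depend on it. It would go too far to say that the paired test produces excess false positives here.

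**What to change.** Replace the single sentence on tests with two. Within-patient change: paired t test, or Wilcoxon signed-rank if its assumptions are not met. Patients versus volunteers: Welch's t test, or Mann-Whitney.

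This changes wording only and needs no further data or participants.

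Optionally, describe the patients' day-28 and day-120 saliva values alongside the volunteers' values as a reference. Table 3 already schedules these patient measurements, so this needs no extra collection either.

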## Discussion

The aim of this phase I study is to evaluate the safety and preliminary efficacy of treatment of xerostomia after irradiation of patients with oropharyngeal carcinoma with allogeneic MSCs derived from umbilical cord tissue. These cells are characterized by a high rate of stemness and marked immunomodulatory activity. Compared with autologous MSCs or allogeneic MSCs from adipose or bone marrow tissue, their collection and processing are less invasive and simpler.^32^ If our hypothesis is confirmed, our results will make an important contribution to the optimization of MSC treatment of xerostomia after radiation and will be used in the design of the next clinical trials.

Treatment of xerostomia after radiation with MSCs is one of the newest therapeutic approaches. Due to the complex pathophysiology of radiation-induced salivary gland hypofunction, which also involves immune mechanisms, MSCs represent an interesting therapeutic agent because they have both immunoregulatory and regenerative effects.^33^ The mechanism of action of MSCs is therefore multifaceted and well suited for the treatment of diseases with a complex etiologic background. Although MSCs are naturally present in affected tissues, their numbers are significantly reduced after irradiation.

The first reports on the treatment of xerostomia with MSCs in animal models appeared about ten years ago. In irradiated mouse models, systemic therapy with adipose-derived MSCs was shown to improve salivary flow.^34^ Following therapy, there was an increase in mucin secretion and amylase production.^35^ In addition, MSC therapy affected the architecture of the gland by increasing the number of functional acini and improving the microvascular structure. Compared with the untreated group, MSC-treated mice had a lower number of apoptotic cells, confirming the known anti-apoptotic and mitogenic effects of MSCs.^35,36^

There is less clinical evidence for the efficacy of xerostomia therapy with MSCs compared with some other indications, e.g., orthopedics or hematology. However, significant progress has been made in recent years. In 2018, Grønhøj *et al*. were the first to publish the results of a phase I/II clinical trial evaluating the safety and efficacy of therapy for xerostomia after RT with autologous MSCs.^37^ They performed a randomized, placebo-controlled trial in 30 patients with squamous cell carcinoma of the oropharynx who had been cured with (chemo)radiotherapy two or more years ago. MSCs were applied to both submandibular glands under ultrasound guidance. The amount of cells (drug dose) was calculated using available preclinical data, taking into account gland volume in humans. The maximum dose of MSCs was approximately 4.5×10^7^ MSCs per gland (2.86×10^5^ – 2.86×10^6^ MSCs/cm^3^ of gland). No side effects were observed during the study and up to two years after treatment. Compared to the placebo group, the treated group showed a statistically significant increase in unstimulated salivary flow both one month (33% increase, p=0.048) and four months after treatment (50% increase, p=0.003). Four months after MSC application, treated patients reported significant improvement in xerostomia symptoms (VAS questionnaire) compared to the placebo group. In a subsequent report with a median follow-up of 3.6 years after treatment, the authors reported no serious adverse events associated with the intervention, but maintained a positive clinical effect of MSC treatment.^38^

In addition, Lynggaard *et al*. published encouraging results on the treatment of radiation-induced xerostomia with allogeneic adipose-derived MSCs.^39^ The use of allogeneic MSCs offers numerous logistical advantages: surgical intervention is no longer required to obtain the starting material, and the quality of the final preparations can be better controlled.^40^ In this study, 25×10^6^ MSCs were inserted into each submandibular gland and 50×10^6^ MSCs were inserted into each parotid gland in ten patients; the follow-up period was four months. During this period, an increase in mean unstimulated salivary flow was measured from an initial 0.13 ml/min to 0.18 ml/min. Stimulated salivary flow also increased after therapy from 0.66 ml/min to 0.75 ml/min. Patients’ subjective perception of an improvement in xerostomia was confirmed by questionnaire results, and no serious adverse events were reported during the study period.^39^

Recently, a dose-escalating phase I study protocol (3 + 3 design) was published for the treatment of radiation-induced xerostomia in patients with head and neck cancer with interferon-gamma-stimulated autologous bone marrow stromal cells.^41^ The results of this study are not yet available. However, in a pilot study, the same group has already used MSC prepared in this manner in six patients who received a single injection of 10×10^6^ MSC into a single mandibular salivary gland and found that the therapy was well tolerated and showed a trend toward improvement in salivary volume and quality of life.^42^

To our knowledge, there has been no research using allogeneic MSCs from umbilical cord tissue. We believe that this may have several advantages. First, the collection of umbilical cord tissue is noninvasive for both the patient and the donor. The relative ease of obtaining umbilical cord tissue allows for greater flexibility in cryobanking “off the shelf” MSC products. This is also accelerated by the biological advantages of MSCs from umbilical cord tissue compared with, for example, bone marrow or adipose tissue, namely their high proliferation rate, smaller cell size, and lower rate of senescence during cell culture, which allows for higher cell yield during manufacturing.^32,43^ Last but not least, umbilical cord tissue-derived MSCs have been reported to have excellent immunomodulatory potential, very low immunogenicity, and documented regenerative properties that may outperform tissue-derived MSCs in certain aspects.^44,45^ Because this is an academic clinical trial focusing on a very limited number of patients, we chose a single dose consistent with previous report of safe use of allogeneic adipose-derived MSCs for the treatment of xerostomia.^39^ We believe that this is also a safe dose, both because of the small cell size of MSCs from umbilical cord tissue and because of their low immunogenicity profile.^46^

Because this is the first attempt to evaluate the use of MSCs from umbilical cord tissue for the treatment of xerostomia, we made every effort to design our study to be as similar as possible to the designs of previously published studies. For example, we used comparable study inclusion criteria (oropharyngeal cancer, at least 2 years after RT, and no evidence of recurrence) and exclusion criteria, examinations (unstimulated and stimulated salivary flow measurements with salivary composition analysis; biopsy, MRI, and US of the salivary glands; questionnaires on xerostomia and quality of life), and time points for assessing treatment effect (4 weeks and 4 months after procedure).^39,41,47^ The nuclear medicine studies in our protocol aim to provide additional definition of the effect of the administered therapy. This should enable us to make a more credible comparison of our results with those of other authors, which will undoubtedly help to evaluate the potential of our approach compared with previously studied methods for the treatment of xerostomia after irradiation with MSCs.

## Conclusions

The treatment of xerostomia after irradiation with MSCs represents a promising new therapeutic method, which is expected to trigger the regeneration of the glandular tissue and improve its function, with a positive impact on patients’ quality of life. Moreover, a crucial aspect is the fact that no serious adverse effects related to MSC therapy have been observed up to 3.6 years (median) after this type of treatment in the clinical trials performed so far.^32^ We expect that the results of our study will contribute significantly to a deeper understanding of the effects of treatment with allogeneic MSC from umbilical cord tissue and optimize this therapy. The research results will not only be valuable from a scientific or academic point of view but will also have practical and clinical significance.
